### Sample size calculation

To compare the studied variables between the two groups, considering the error of 5%, the power of 80%, and the effect size of 0.8 (based on Cohen's criterion), the minimum sample size is equal to 26 people in each group and a total of 52 people will be determined.

*t tests—Means*: Difference between two independent means (two groups)

*Analysis:* A priori: Compute required sample size

*Input:* Tail(s) = Two

Effect size d = 0.80

α err prob = 0.05

Power (1-β err prob) = 0.8

Allocation ratio N2/N1 = 1

*Output*

Noncentrality parameter δ = 2.8844410

Critical t = 2.0085591

Df = 50

Sample size group 1 = 26

Sample size group 2 = 26

Total sample size = 52

Actual power = 0.8074866

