### Study design

A diagram of the study design is demonstrated in Fig. 1. A flow chart of the study process is demonstrated in Fig. 2. A total of 52 patients with NAFLD will be screened based on the inclusion criteria. After participant recruitment from online advertisements and social media, 52 participants who meet the eligibility criteria will be enrolled for the trial. We used stratified block randomization with a block size of 2 Patients will be randomly assigned to either an intervention or control group based on BMI (25–30 and 30–35) and gender (male or female). First, we select patients who meet the criteria. Then that variable is used to match the next person with the first person. After all, two patients with similar characteristics are in the same block. Finally, two subjects in the same block are randomly assigned to either the IF diet or the low-calorie diet using random assignment software. All individuals who meet the inclusion criteria and voluntarily participate in the study will receive complete information regarding the purpose of the study, the type of intervention, and the duration of the study. Then, written informed consent will be obtained from individuals. The current clinical trial will be done based on the Helsinki Declaration. All participants will be informed that all services will be free of charge and that they can withdraw from the study at any time. Each person will be given a pre-made meal plan booklet with a set of menus and recipes for breakfast, lunch, dinner, and snacks based on the recommended diet.

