### Statistical analysis

Statistical data will be analyzed using SPSS software version 22. The results will be reported as mean ± standard deviation (SD). The normality of variable distributions will be checked using the Kolmogorov–Smirnov test. If a variable does not follow a normal distribution, a logarithmic transformation will be applied. The independent t-test will be used to compare the consumption of food and nutrients between the two groups, and the chi-square test will be used to compare qualitative variables between the two groups. The analyses will be performed based on the intention-to-treat (ITT) approach. Missing values will be treated according to the linear regression method. ANCOVA with adjustment with baseline values will be used to assess the effect of intervention on dependent variables. *p*-value < 0.05 will be considered statistically significant.

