### Strengths and limitations

This is the first clinical trial to assess the effects of the 16:8 IF diet in comparison with LCD on lipid profile, glycemic status, and liver fibrosis in patients with NAFLD. It should be noted that this procedure is inexpensive and the patient will not incur additional costs. We will use stratified block randomization to match participants based on several confounding variables that may affect the results. People, moreover, will participate via public announcements. Therefore, all participants can be eager to comply with dietary recommendations. Some limitations need to be considered. First, we will assess adherence to the IF diet through self-reported food recalls. Therefore, self-reporting of food consumption may influence study results. Second, although FibroScan has been established as a noninvasive and reliable method for diagnosing fibrosis and steatosis in NAFLD patients, the gold standard for assessing liver steatosis is magnetic resonance imaging-proton density fat fraction (MRI-PDFF). Third, we will assess physical activity using a physical activity questionnaire. Fourth, stool sample measurements will not be performed in this study. Therefore, dysbiosis of intestinal flora cannot be measured. Eventually, we have no access to bio-electrical impedance analysis (BIA) to examine body composition in this study.

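### Randomisation is balanced on BMI class and sex, but the stated ANCOVA names neither factor, so the test is conservative to the extent that they still predict outcome after baseline adjustment

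*Protocol article*

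**What the plan says.** Three places in the protocol article bear on this.

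- **Study design** sets the allocation: "We used stratified block randomization with a block size of 2". The strata are "based on BMI (25–30 and 30–35) and gender (male or female"), which makes four cells. Two patients alike on these factors form a block, and then "two subjects in the same block are randomly assigned to either the IF diet or the low-calorie diet".
- **Strengths and limitations** gives the reason: "We will use stratified block randomization to match participants based on several confounding variables that may affect the results".
- **Statistical analysis** gives the effect model: "ANCOVA with adjustment with baseline values will be used to assess the effect of intervention on dependent variables". It has no term for BMI class, sex or block, and no other section brings these factors into the analysis.

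The **Sample size calculation** treats the arms as two independent means, with 26 per group, d = 0.80, two-sided, "α err prob = 0.05" and "Actual power = 0.8074866".

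**The concern.** Blocks of two within strata make the arms almost identical in BMI class and sex. Whatever these factors contribute to the outcome therefore cancels out of the difference between diets. The ordinary ANCOVA standard error does not know this. It is built from the residual variance, and if the strata are left out, their contribution stays in that residual. The model then reports more uncertainty than the design has.

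The result is a test that rejects less often than 5% under the null, intervals that are wider than they need be, and a lower chance of detecting a real difference than the same 52 patients could give. The size depends wholly on how much the strata explain once the baseline value of the outcome is in the model.

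**Working it through.** **1. The plan's own figure.** With n = 26 per group and d = 0.80, the noncentrality is 0.80 × √(26/2) = 2.8844, df = 50 and the critical t is 2.0086. Noncentral t power is 0.8075. The stated 52 patients and power of 0.8074866 reproduce exactly.

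**2. Formula.** Let R² be the share of the variance left after baseline adjustment that BMI class and sex explain. The documents do not give it, so it is an assumption, shown as a range. Set the variance left after baseline adjustment to 1. With 52 patients split equally:

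- standard error reported without strata ≈ √(4/52) = 0.277
- true standard error under forced balance ≈ √(4/52) × √(1 − R²)
- ratio of reported to true = 1/√(1 − R²)
- type I error ≈ 2 × [1 − Φ(1.96/√(1 − R²))]

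At R² = 0.20 the true value is 0.277 × 0.894 = 0.248, the ratio is 1.118, and the type I error is 2 × [1 − Φ(2.191)] = 2.8%.

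**3. Simulation.** 52 patients were placed in 26 pairs within four strata, with one of each pair to each arm. There were 10,000 runs under the null and 6,000 with an effect of 0.8 SD, in units of the SD left after baseline adjustment. *Without* is ANCOVA on the baseline value alone. *With* adds sex and BMI class as two main effects.

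| Assumed R² | SE ratio (formula) | Type I, formula | Type I, without | Type I, with | Power, without | Power, with |
|---|---|---|---|---|---|---|
| 0 | 1.000 | 5.0% | 5.1% | 5.2% | 79.6% | 79.4% |
| 0.05 | 1.026 | 4.4% | 4.6% | 5.2% | 80.3% | 81.7% |
| 0.10 | 1.054 | 3.9% | 4.1% | 5.3% | 81.4% | 83.6% |
| 0.20 | 1.118 | 2.8% | 2.7% | 4.8% | 82.9% | 88.2% |
| 0.30 | 1.195 | 1.9% | 2.1% | 5.1% | 84.2% | 91.6% |

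The Monte Carlo standard error is about √(0.05 × 0.95/10,000) = 0.2 points for type I error and √(0.8 × 0.2/6,000) = 0.5 points for power. A repeat simulation gave type I error without strata of 5.1, 4.1, 3.9, 3.0 and 2.1%. Its power was 80, 80, 80, 83 and 84% without strata, against 80, 82, 83, 88 and 92% with them.

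**4. The mechanism, seen directly.** At R² = 0.20 the estimate varies from trial to trial with SD 0.249 under both models. Without strata the model reports a mean standard error of 0.279, and with strata 0.249. The two estimates are equally good, but one model overstates its uncertainty by 0.279/0.249 = 1.12.

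**5. Which terms to add.** Two main effects do not cover four strata if sex and BMI class interact. When the interaction carries a third of the stratum variance at R² = 0.30, the main-effects model stays conservative, with type I error about 3.6%. Adding the interaction brings it to about 4.8%. A within-pair analysis also holds the nominal level but has less power than the main-effects model: 86.2% against 88.2% at R² = 0.20, and 76.5% against 79.4% at R² = 0.

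**The case against.** Much of the case for leaving the model alone is fair.

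- **The loss is conditional.** At R² = 0 nothing is lost, and at 0.05 the loss is trivial. The article says only that the factors may affect the results, not that they still do once the outcome's own baseline is in the model. Eligibility is limited to BMI 25 to 35, so the BMI stratum splits a narrow range. For weight, BMI and waist, the baseline value already carries much of the BMI information. All of this stands.
- **The trial is not underpowered by this.** A reader might infer that 52 patients no longer suffice or that the benefit of stratifying is thrown away. The figures do not support that. Without strata, power stays at about 80 to 84%, near or above the planned 0.807, and it rises with R² because the estimate keeps the forced balance. Only part of the benefit is lost.
- **The wording may be elastic.** Sex and BMI are themselves measured at baseline, and a condensed article may leave the full covariate list to another document. This stands in part. The ordinary reading is the baseline of each outcome, and the article does state an adjustment set. If the strata were meant, the same one-line edit says so.

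**Conclusion.** The stated analysis does not follow the stated design, and it should. The direction is certain: if the strata are prognostic after baseline adjustment, the standard error is too large and the test is conservative. The size is not certain. For an assumed residual R² of 0.05 to 0.10 the standard error is 3 to 5% too large and about one to three points of power are given up. At 0.20 to 0.30 it is 12 to 19.5% too large and the cost is about five to eight points. Nothing in the documents says which end applies.

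A reader might take the mismatch to mean that the diet effect is biased or that false positives are inflated. Neither follows: the estimate is essentially unchanged, and the error rate moves below 5%, not above it. The planned sample size stands as calculated.

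The figures assume complete pairs, equally common strata, normal outcomes and an effect of 0.8 SD in units of the SD left after baseline adjustment. The powers with strata come from the two-main-effects model, and a third degree of freedom changes them very little.

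**What to change.** In the Statistical analysis section, replace the ANCOVA sentence, for continuous outcomes, with:

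> ANCOVA with terms for arm, the baseline value of the outcome, and the four randomisation strata (sex by BMI class as used at randomisation).

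Use the stratum recorded at allocation, and settle the wording before outcome data are compared by arm.

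The change uses 3 degrees of freedom, taking the residual from 49 (52 − 3) to 46. The critical t is 2.0129 at 46 df and 2.0086 at 50 df, a ratio of 1.002, so intervals widen by at most about 0.2% if the strata explain nothing. Both factors are already collected, so no data collection is added. Covering all four cells keeps the nominal error rate if sex and BMI class interact. A pair term is not needed: the blocks are matched on these two factors, and a within-pair analysis costs some power.

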## Discussion

Obesity resulting from excessive calorie intake is a major risk factor for insulin resistance (IR), which is a key factor in the development of metabolic syndrome and type 2 diabetes [29]. IR promotes the development of NAFLD in a subgroup of patients, which can progress to a more severe form, namely NASH [30]. Despite weight loss, there is still no consensus on appropriate strategies for managing NAFLD patients, and unfortunately, our knowledge of more effective treatment options to minimize or its removal remains limited [31, 32]. Many guidelines support recommendations on risk factor control and lifestyle changes, including diet and physical activity [33]. Furthermore, for the treatment of obesity and metabolic parameters, energy restriction can be considered as the main mechanism [34]. Energy restriction in an IF diet can lead to the mobilization of free fatty acids, increased fat oxidation, and thus the generation of ketone bodies [22]. Despite this, a study conducted by Santos HO and colleagues showed that IF has beneficial effects on lipid metabolism at the molecular level [35]. By reducing apolipoprotein B (apoB) production, increasing fatty acid oxidation, and reducing TG content in the liver, IF may help improve lipid profiles and reduce the risk of metabolic diseases [35]. On the other hand, because NAFLD and atherosclerotic dyslipidemia are related to each other [36], recent studies have shown that IF leads to a decrease in the levels of very low-density lipoprotein cholesterol (VLDL_C), LDL_C, and small dense low-density lipoprotein cholesterol (sdLDL_C), highlighting the anti-atherogenic effects of IF diets [35, 37]. In individuals, moreover, with NAFLD, liver function enzymes (AST, ALT, and GGT) are commonly considered in clinical assessment. Johari and colleagues after 8 weeks of calorie restriction, observed a reduction in AST and ALT levels in patients with NAFLD [33]. The authors described this reduction in liver tests as an improvement in steatosis or visceral fat in the liver [33].

The results of this study can be applied to the management of NAFLD patients. Because dietary modification is likely the most cost-effective method for disease management and treatment, the results of our study can be widely used by hepatologists and nutritionists.

In conclusion, because dietary modification is most likely a cost-effective method of disease management and treatment, the results of this study can be applied to the management of NAFLD patients.

### Strengths and limitations

This is the first clinical trial to assess the effects of the 16:8 IF diet in comparison with LCD on lipid profile, glycemic status, and liver fibrosis in patients with NAFLD. It should be noted that this procedure is inexpensive and the patient will not incur additional costs. We will use stratified block randomization to match participants based on several confounding variables that may affect the results. People, moreover, will participate via public announcements. Therefore, all participants can be eager to comply with dietary recommendations. Some limitations need to be considered. First, we will assess adherence to the IF diet through self-reported food recalls. Therefore, self-reporting of food consumption may influence study results. Second, although FibroScan has been established as a noninvasive and reliable method for diagnosing fibrosis and steatosis in NAFLD patients, the gold standard for assessing liver steatosis is magnetic resonance imaging-proton density fat fraction (MRI-PDFF). Third, we will assess physical activity using a physical activity questionnaire. Fourth, stool sample measurements will not be performed in this study. Therefore, dysbiosis of intestinal flora cannot be measured. Eventually, we have no access to bio-electrical impedance analysis (BIA) to examine body composition in this study.

## Data Availability

Data generated or analyzed during the current study will be available from the corresponding author upon reasonable request.
